## PART I: GOALS AND STATE-OF-THE-ART

### INTRODUCTION

Brain lesion is the most prevalent cause of physical disability: cerebral palsy occurs in 1 out of 500 neonates (Graham, 2016) and stroke events are projected to affect 1 in 4 people over age 25 according to the World Stroke Organization. The consequences of brain injury are highly variable and usually include motor disorders (walking or grasping difficulties) resulting in long-term functional deficits (daily living activities such as dressing, eating, toileting ...), thereby limiting patients' autonomy.

Traditional neurorehabilitation for patients with motor disabilities consists of physical/occupational therapy sessions of less than an hour a few times a week while patients try to keep on with their activities of daily life (ADL) according to their physical capabilities. Motor training is a crucial component of neurorehabilitation as it may induce recovery through brain plasticity and thereby may partly reverse the damage at the origin of the motor impairment. It has recently become apparent that *intensive* motor training exhibits higher efficiency than traditional non-intensive neurorehabilitation, across age groups and disability levels (Bleyenheuft, Arnould, et al., 2015; Bleyenheuft et al., 2017; Bleyenheuft & Gordon, 2014; Hatem et al., 2016; Pollock et al., 2015).

We aim to show for the very first time that HABIT-ILE, an intensive rehabilitation program developed at UCLouvain in collaboration with a team at Columbia University, improves the recovery of motor control capabilities in two distinct populations in which intensive therapies have so far been very little studied: (i) newborns with CP and (ii) adults with chronic post-stroke disabilities. HABIT-ILE is likely to induce larger microstructural changes in the brain white matter (WM), in tracts not only involved in motor function but possibly in other functions as well (such as movement planning), treating the causes of the disability rather than the symptoms and potentially improving the efficiency of neurorehabilitation.

Whether in traditional or in intensive neurorehabilitation, each brain-lesioned patient should follow a program specifically tailored to their initial disability, their expected level of motor recovery and the actual chances of achieving the desired recovery, within the practical limits of a clinical context such as time, cost and personnel. It is therefore crucial to understand the nature and extent of brain damage, to identify the (un-)damaged areas that can be adaptively healed through WM plasticity, those that remain beyond recovery and those which can predict recovery before improvements in motor function occur.

Modern neuroimaging techniques, in particular diffusion-weighted magnetic resonance imaging (DW-MRI), have the potential to improve our understanding of the link between brain structure and motor recovery, especially as neuroplastic changes occur. Recent advances in brain microstructure ( $\mu S$ ) estimation from DW-MRI obtained at ICTeam jointly with teams at the Ecole polytechnique fédérale de Lausanne (EPFL, Prof. [name]) and Harvard Medical School (HMS, Prof. [name]) offer new ways to non-invasively assess plastic changes in the damaged human WM. The theoretical promise of these advanced mathematical models of the DW-MRI signal is the characterization of the brain white matter at the micrometer level, providing indices reflective of the morphometry of axons, myelin sheaths and glial cells generically referred to as indices of the *microstructure*. The exact biological interpretation of these indices is subject to debate and validation is an ongoing quest. Nonetheless, compared with the phenomenological indices derived from the diffusion tensor imaging (DTI) model (Basser et al., 1994) traditionally used in neurorehabilitation studies, these novel approaches have the potential to provide more specific insights into the structural alterations of the brain WM  $\mu S$  underpinning (a) motor impairments and (b) the response to therapy, with the promise of developing more predictive biomarkers to guide neurorehabilitation.

---

 <https://www.world-stroke.org/about-wso/wso-annual-report>

During the two proposed randomized controlled trials (RCTs), high-quality, quantitative data will be collected in both CP infants and stroke adults before and after intensive neurorehabilitation with HABIT-ILE. First, clinical scores will be collected following well-established and validated assessments. Second, biomechanical data will be acquired. In the CP study, it will consist of optoelectronic motion capture measurements. In the chronic stroke study, it will be obtained on the REAplan® bimanual neurorehabilitation robot installed at CHU UCL Namur (Mont-Godinne). Third, neuroimaging will be performed, for both populations, on the new 3-Tesla GE MRI scanner installed at Cliniques Universitaires UCL Saint-Luc in the fall of 2019. Conventional MRI such as T1 and T2 will be supplemented with advanced DW-MRI leveraging the new scanner's capabilities. A number of mathematical models, from traditional DTI to our latest developments, will be fitted to the DW-MRI data to produce whole-brain maps of WM microstructural indices in complement to global WM connectivity maps.

This project is a unique opportunity to investigate the difference induced by intensive neurorehabilitation in the  $\mu S$  of the brain and to understand the specificity of changes in mature and immature brain to better target the components needed to induce neuroplasticity and functional recovery in each. Our efforts will also lead to the creation of an outstanding data set of DW-MRI signals and the related evaluations of motor capabilities, for both adults and children with acquired brain damage leading to life-long motor impairments. It will also set the foundation of a multidisciplinary platform for the development of neuroimaging tools. The global outreach of this project will therefore extend far beyond the walls of our research facilities at UCLouvain.

## GRAND CHALLENGES OF THE RESEARCH

The grand challenges addressed by this project are four-fold and intrinsically multi-disciplinary:

1. The mathematical models studied at ICTEAM are based on sound biological descriptors and are likely to exhibit increased *sensitivity* to neuroplastic changes. More fundamentally, more validation is needed to determine the *specificity* of these models and what exactly they can "see" in the WM microstructure ( $\mu S$ ). Popular models claiming biophysical specificity like NODDI may have shown increased sensitivity and prediction power than traditional DTI indices in a few cases but their specificity is still debated on theoretical grounds as well as on empirical grounds, both in animal and in human studies. The two clinical trials proposed in this project will constitute a platform to compare DW-MRI models ranging from the traditional DTI to our latest developments such as DIAMOND and Microstructure Fingerprinting. Sensitivity will be assessed via the ability to predict the motor recovery of patients and via differences between patients following intensive neurorehabilitation and patients receiving their usual treatment. Specificity will be informed by the location and extent of WM changes (e.g. in motor tracts), their nature (e.g. loss of axons, change in axonal caliber due to demyelination) and the consistency between the two age groups (infants vs adults). The best MRI-derived microstructural indices will be combined with other baseline clinical and biomechanical scores via advanced multi-agent algorithms to provide the most predictive biomarker of motor recovery.
2. Intensive motor skill training programs designed by Prof. [name]'s team at IoNS in collaboration with the team of Prof. [name] at Columbia University improve the motor abilities of school-age children with uni- and bilateral cerebral palsy. Traditional DTI indices have suggested that this improved motor outcome was, among others, related to a better overall quality of white matter axons in the corticospinal tract (CST), the primary pathway for producing voluntary movements. However, no DW-MRI approach has been able to test for finer structural alterations such as the myelination or the packing density of axons in the CST. In addition, the benefits of this neurorehabilitation method have not been yet evaluated in infants under 2 years old when neural connectivity undergoes particularly active development. Intensive motor training may have a far greater impact in this group and may prevent most of the brain damage causing the disability.

3. Elucidating the exact nature and evolution of defects in neural connectivity and  $\mu S$  occurring after stroke in adults and correlating it with motor function recovery is a pressing issue at IoNS. Stroke involving the motor system and especially the CST leave many stroke survivors with motor deficits and chronic impairments. The impact of a *unilateral* stroke on *bimanual* motor control and activities of daily life (ADL) are overwhelming, deserving special attention in the design of rehabilitation programs. Recent research on animal models and children with CP suggests that even in a chronic phase, specific interventions such as HABIT-ILE can drive large motor improvements and structural repair in the damaged CST (McKenzie et al., 2014; Sampaio-Baptista et al., 2013). Such interventions are based on intensive motor skill learning concepts (Byblow et al., 2015; Krakauer, 2015; Winters et al., 2015). However, it is unknown whether such functional changes could be obtained in adults, whether similar changes could be observed in the CST or whether these changes would be different in nature than those observed in infants. Novel DW-MRI markers provided by ICTEAM will help clarify the link between brain  $\mu S$  after stroke and improvement after intensive rehabilitation, headed by Prof. [name] (IoNS / Stroke Unit of the CHU UCL Namur, Mont-Godinne).
4. The identical experimental settings of WP 2 and 3 allow us to directly compare WM  $\mu S$  baseline damage and training-induced microstructural changes between hemiplegic CP infants and adult stroke patients, both at the macroscopic level using whole-brain tractography and at the microscopic level using voxel-wise, model-based microstructural features. The deep underpinning of the differential repair mechanisms based on the initial conditions and age of the patients is likely to bring neurophysiological responses to the conditions enabling WM repair. Investigating the best responders depending on initial conditions should help better tailor treatment to each patient.

Our workplan will rely on several research hypotheses which will be explored through a common framework (data-processing-platform) coordinated by [name]. A final clinical toolset will be established, efficiently combining neuroimaging signals and quantitative motricity signals measured clinically during rehabilitation programs. IoNS and ICTEAM have had several collaborations in the fields of neuroimaging and in the practical use of augmented reality for rehabilitation (Caby et al., 2011; Noirhomme et al., 2004) and this project is the ideal platform to foster further partnerships. All three principal investigators of this proposal are members of the Louvain Bionics group which connects researchers from science and technology, social sciences and health sciences for the development of rehabilitation tools. This research project also presents a unique opportunity to open a novel avenue of research to the neuroimaging platform at UCLouvain.

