stroke, no change in traditional DTI-derived indices was observed between the lesioned and the contralateral parts of the brain (Adluru et al., 2014). NODDI on the other hand did capture changes as the ND and OD were much *higher* in the stroke area; however the biological interpretation of these two changes was not straightforward (Adluru et al., 2014). In a neuroimaging study of 10 children with unilateral cerebral palsy (Nemanich et al., 2019), while the ND was *lower* in the lesioned CST, as may be expected from the known pathophysiology (see WP 2), the lower OD was more difficult to interpret and was likely a confound of increased extra-axonal space in the WM. NODDI did exhibit better sensitivity than DTI as manual motor function was strongly correlated with the NODDI-derived ND, but not with the FA from DTI (Nemanich et al., 2019). This was likely attributable to its modeling of the diffusion in the tissue which, although imperfect, is more advanced than that of DTI. In the absence of a clear consensus on the biological interpretation of NODDI indices, care should be taken when analyzing brain maps of NODDI indices in human studies where histological verification is not possible.

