### **A multi-modal approach predicts and explains motor recovery (HP1.2)**

The acquisition of data from multiple modalities lies at the core of this project. Patients undergoing neurorehabilitation will be evaluated using well-established and quantitative clinical scales. They will also be subject to biomechanical recordings either through a camera motion capture system (WP 2) or using a specifically-designed neurorehabilitation robot (WP 3). Each patient’s trajectory will therefore be thoroughly documented with a massive amount of data which our team at ICTEAM will mine using the latest advances in data analysis. Indices pertaining to different feature spaces (clinical scores, biomechanical measurements and neuroimaging) collected before treatment will complement each other to provide biomarkers able to quantify patients’ motor and function recovery.

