We propose an evaluation of the effects of HABIT-ILE in 6-18 month old infants based on a comprehensive functional, neurological and biomechanical assessment. HABIT-ILE is an intervention based on motor skill learning principles which focuses on the bimanual use associated to postural and/or gross motor stimulation (Bleyenheuft & Gordon, 2014). Its efficiency has already been demonstrated for both upper and lower extremities in children with unilateral (Bleyenheuft, Arnould, et al., 2015) and bilateral CP (Bleyenheuft et al., 2017) between 6 and 18 years old. **We aim to show for the first time that HABIT-ILE prevents secondary motor damage in 6-18 month old infants by treating one of its causes.**

We aim to demonstrate the effectiveness of HABIT-ILE in preventing secondary damage in CP children. More specifically, we will test the following research hypotheses. In infants with unilateral CP:

1. the HABIT-ILE intervention induces superior, clinically meaningful gains on both activity limitations (primary functional outcome) and impairments (**HP2.0**)
2. The HABIT-ILE intervention induces an increase in myelination evidenced by a change in white matter microstructure integrity of the CST and cortico-cortical connections as measured from DW-MRI (primary imaging outcome), a decrease in brain inflammation, an increase in CST projections to the spinal cord, and prevents CST reorganization in the affected hemi-cortex of infants with unilateral CP (**HP2.1**)
3. the changes in WM- $\mu$ S integrity correlate with mid-term changes in clinical outcomes (follow-up) (**HP2.2**)
4. the functional gains will be predicted by baseline WM- $\mu$ S integrity (**HP2.3**)

5. therapy onset in the course of infants development might influence long-term neuroplastic and functional changes, earlier onset might induce larger changes (HP2.4)

[figure not shown]

Figure 3: Design of the randomized controlled trial for a population of infants with cerebral palsy.

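### Baseline prediction of recovery scores prognosis, not sensitivity to neuroplastic change; arm differences score that sensitivity only if HABIT-ILE alters white matter

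*Protocol*

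**What the plan says.** In the protocol's Grand Challenges of the Research, item 1, the models are described as "likely to exhibit increased *sensitivity* to neuroplastic changes". The same item fixes how this is judged: "Sensitivity will be assessed via the ability to predict the motor recovery of patients and via differences between patients following intensive neurorehabilitation", the comparison group being patients on their usual treatment. It gives no rule for combining the two criteria. The best indices then join other baseline clinical and biomechanical scores "to provide the most predictive biomarker of motor recovery".

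The timing of the predictors is stated elsewhere. HP1.2 speaks of indices "collected before treatment will complement each other to provide biomarkers". HP2.3, for infants, says "the functional gains will be predicted by baseline" microstructural integrity, and HP3.3 says the equivalent for the corticospinal tract (CST) in adults.

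Whether HABIT-ILE changes white matter is itself under test, as HP2.1 in infants and HP3.1 in adults. For adults, item 3 of the Grand Challenges concedes that "it is unknown whether such functional changes could be obtained in adults, whether similar changes could be observed in the CST".

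Change-based analyses are planned too. HP2.2 and HP3.2 relate change in the indices to mid-term clinical change, and both Statistical Analysis sections compare neuroplastic changes between groups. Item 1 does not name the HP2.2/HP3.2 analysis as a measure of sensitivity.

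**The concern.** The property claimed is responsiveness: when tissue changes, the index moves. A value taken once, before treatment, cannot show that. A baseline index may predict who recovers because it reflects the extent of the lesion, and it would do so equally well if it never moved again. Calling that result sensitivity to neuroplastic change attaches a conclusion about change to evidence that contains none.

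The arm-difference criterion does concern change, but its reading depends on a second unknown. If the arms do not differ on an index, either the index is insensitive or there was no white matter change to detect, and this criterion alone cannot separate the two. At stake is Grand Challenge 1's comparison of models from DTI to Microstructure Fingerprinting. A model could be called more sensitive to plasticity because it is prognostic, or insensitive because the therapy had no effect on white matter.

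**Working it through.** The plan states no figure on this point, so there is none to reproduce. The argument is logical; the numbers only illustrate it.

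**Step 1: what each criterion needs.**

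| Criterion in item 1 | Scans needed | Must the index change? | Must HABIT-ILE change white matter? |
|---|---|---|---|
| Predicting recovery | Baseline only (HP1.2, HP2.3, HP3.3) | No | No |
| Arm difference in index change | Baseline and later | Yes | Yes (HP2.1, HP3.1) |

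**Step 2: inputs.**
- From the protocol: 24 patients per arm in each trial, 48 in all. A smaller case of 17 per arm reflects the stated success rate of at least 70% for repeated infant MRI: 0.70 × 24 = 16.8.
- Assumed, because the protocol gives no values: correlation r between baseline index and recovery of 0, 0.3 or 0.5, and a true effect on white matter change of 0 or 1 SD.
- Tests: Pearson correlation over all patients and a two-sample t-test on index change, each at two-sided 5%. There were 3,000 simulated trials per setting.
- A static index has between-scan change that is pure noise. A perfect index tracks true change exactly. For a noisy index, half the variance of change is true change.

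**Step 3: results (share of trials significant).**

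| Index | True effect | Prediction, 24/arm | Arm difference, 24/arm | Prediction, 17/arm | Arm difference, 17/arm |
|---|---|---|---|---|---|
| Static, r = 0.5 | 1 SD | 96% | 5% | 89% | 5% |
| Static, r = 0.3 | 1 SD | 56% | 5% | 42% | 5% |
| Perfect, r = 0.5 | 0 | 96% | 5% | 88% | 5% |
| Perfect, r = 0 | 0 | 4% | 5% | 5% | 4% |
| Perfect, r = 0 | 1 SD | 6% | 92% | 6% | 82% |
| Noisy, r = 0 | 1 SD | 5% | 67% | 5% | 52% |

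If only the 24 patients of one arm are used, prediction at r = 0.5 is significant in 73% of trials.

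**Step 4: hand check.** Power for a correlation is approximately Φ(atanh(r) × √(n − 3) − 1.960).
- r = 0.5, n = 48: 0.5493 × 6.708 = 3.685, and Φ(3.685 − 1.960) = Φ(1.725) = 0.958.
- r = 0.3, n = 48: 0.3095 × 6.708 = 2.076, and Φ(0.116) = 0.546.

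For the arm difference, the standardised effect times √(24/2) is 1 × 3.464, and Φ(3.464 − 1.960) = Φ(1.504) = 0.93. The t-test is slightly lower, which agrees with the simulated 92%.

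**Step 5: reading.** The prediction column follows r alone and is blind to whether the index can move. With a real effect, the arm-difference column orders the indices correctly: 92%, 67%, 5%. With no effect, a perfect and a static index, both at r = 0.5, have the same profile (96% and 5%), and neither criterion separates them.

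**The case against.** Several points on the other side are sound.

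- *Both criteria are named.* A reader might infer that an index that never moves could be declared the winner outright. The protocol does not say that prediction alone suffices, and a static index passes the arm comparison only at the 5% error rate. Nor does the protocol say that both must be met. The point is therefore confined to what the prediction criterion measures.
- *Arm differences are a fair comparison.* A reader might infer that neither criterion measures sensitivity to change. That goes too far. All models can be fitted to the same scans, so whether HABIT-ILE works is common to all of them. If it does, randomised arm differences rank responsiveness; if it does not, the comparison is uninformative but favours no model.
- *Prediction is a legitimate goal.* HP1.1 to HP1.4 are all framed around predicting and explaining recovery, so choosing indices for prediction suits them. This stands: the error lies in the label, not in the analysis.
- *The NODDI paragraph.* It says "NODDI did exhibit better sensitivity than DTI as manual motor function was strongly correlated with the NODDI-derived ND, but not with the FA from DTI", and a reader might infer that these trials will pick a winner by which index reaches significance. That passage summarises a published study of 10 children and urges care. It shows how the word is used and sets no decision rule, so false-winner rates built on such a rule cannot be charged to this plan.
- *Responsiveness is partly covered.* HP2.2 and HP3.2 address index change, and hardware-based sensitivity studies will be repeated. The former belong in the fix. The latter, as described, address uncertainty in axon diameter rather than response in patients.

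**Conclusion.** The point holds in a limited form. Item 1 counts ability to predict recovery as evidence of sensitivity to neuroplastic change, while the plan's own hypotheses make that prediction from pre-treatment scans. That is prognostic value. Under assumed correlations of 0.3 to 0.5, an index with no responsiveness would be significant in 56% to 96% of trials of 48 patients. Those rates move with the assumed correlation; the logic does not depend on them.

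The arm-difference criterion is valid but conditional. It speaks to sensitivity only if HABIT-ILE truly alters white matter, so a null result there is not evidence that a model is insensitive. The documents do not support the wider claims that both criteria are worthless or that a static index would be named the best model.

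**What to change.** In Grand Challenges of the Research, item 1:

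1. Report prediction of recovery from baseline indices as prognostic value only.
2. Base any statement on sensitivity to change on the change-based measures already planned: arm differences in index change, and index change against clinical change under HP2.2 and HP3.2.
3. State that such a conclusion is conditional on a real white matter change, and that a null arm difference does not show an insensitive model.
4. Compare models on the same patients by the paired difference in the standardised measure with a bootstrap confidence interval, keeping each patient's values from all models together when resampling.

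A cross-sectional score, such as damaged minus undamaged CST at T0, should not take the place of these measures. An index that never changes can do well on it, and dividing by short-term within-patient variability would reward indices that do not move. Its truth is not assured either: the stroke trial admits lesions of any type, size and location, and Grand Challenge 4 cites reduced FA in both CSTs in unilateral CP. The NODDI section also cites an apparent rise in axon density where histology suggested loss, so a score based on the size of a difference could reward the wrong direction.

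The cost is wording and analysis code; every scan needed is already planned. The downside is that, if no white matter change occurs, the project can draw no conclusion about which model is more sensitive to change.
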